**Methods:**

A preliminary German version has been created from the original CCAS Scale using a standardized translation procedure. This version has been pre-tested in cerebellar patients and healthy controls including medical experts and laypersons to ensure that instructions are well understandable, and that no information has been lost or added during translation. This preliminary German version will be validated in a minimum of 65 patients with cerebellar disease and 65 matched healthy controls. We test whether selectivity and sensitivity of the German CCAS Scale is comparable to the original CCAS Scale using the same cut-off values for each of the test items, and the same pass/ fail criteria to determine the presence of CCAS. Furthermore, internal consistency, test-retest and interrater reliability will be evaluated. In addition, construct validity will be tested in a subset of patients and controls in whom detailed neuropsychological testing will be available. Secondary aims will be examination of possible correlations between clinical features (e.g. disease duration, clinical ataxia scores) and CCAS scores.

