## Background

Cerebellar disease results in well-known motor performance deficits, including ataxia of stance and gait, limb incoordination, dysarthria, and oculomotor abnormalities. During the last decades, there has been growing evidence that cerebellar disease is not only accompanied by motor disturbances but also by cognitive and affective symptoms (see [1–3] for reviews). As early as 1998, Schmahmann and Sherman introduced the *Cerebellar Cognitive Affective/ Schmahmann Syndrome (CCAS)* [4]*.* The core symptoms of CCAS are difficulties with executive, linguistic and visuospatial functions as well as problems with the regulation of emotion and affect. Since its original description, evidence for the presence of CCAS has been accumulating in pediatric and adult patients suffering from different cerebellar diseases including various hereditary ataxias, cerebellar tumors, and cerebellar stroke [1–3]. In recent years, advances in structural and functional brain imaging allowed for detailed mapping of cognitive functions in the posterolateral cerebellar hemisphere [5–9]. As yet, diagnosis of CCAS relies on non-standardized bedside cognitive examination and, if available, detailed neuropsychological test batteries. Until recently, there has not been a validated bedside test that was able to reliably screen for CCAS in cerebellar patients – unlike well-established bedside tests for dementias or mild cognitive impairment (MCI), i.e. Mini Mental State Examination (MMSE) or Montreal Cognitive Assessment (MoCA). However, MMSE and MoCA are of limited use to screen for CCAS because cerebellar patients frequently perform within the normal range [10]. Recently, Schmahmann and colleagues [10] have developed a bedside test designed to screen for CCAS in adults. In order to develop this CCAS Scale, they first applied a broad battery of 36 well-established neuropsychological tests in a large group of cerebellar patients primarily suffering from cerebellar degeneration. In the novel CCAS Scale, tests were implemented which captured the core cognitive domains of CCAS, distinguished best between cerebellar patients and controls, and at the same time were short and easy enough to be applied in a bedside setting. These include test items for semantic and phonemic fluency, category switching, verbal registration and delayed verbal recall, digit span forward and backward, cube draw and copy, similarities, go/ no-go, and affect. Single tests can either be passed reaching a specific cut-off score or failed. CCAS is considered possible if one test is failed, probable if two tests are failed, and definite if three or more tests are failed. Version A of the CCAS Scale has then been validated in another US-American cohort of 39 adult cerebellar patients, including patients with cerebellar degeneration and focal cerebellar lesions and 55 matched healthy controls. It exhibited high values for selectivity [that is the ability to distinguish between patients and controls, or in other words preventing controls from being diagnosed as patients; possible/ probable/ definite CCAS: 78/ 93/ 100%] and reasonable sensitivity [that is the probability that a patient is identified as a patient; possible/ probable/ definite CCAS: 95/ 82/ 46%]. Furthermore, it showed modest internal consistency using Cronbach’s alpha value (= 0.59) indicating that no test item within the scale measures the exact same domain(s) as another item. Thus, no test item is redundant. Comparing patients with pure cerebellar lesions and patients with additional extracerebellar involvement the authors found that difficulties in verbal registration and delayed verbal recall were more prominent in the latter. Therefore, poor performance in these two test items is indicative of extracerebellar involvement (“red flag”). In addition to the pass/ fail criteria which are used to screen for CCAS, a total sum score is calculated which allows for follow-up examinations in individual patients [10]. Three parallel versions B-D were developed to enable repeated assessments. In the present study preliminary German versions of the CCAS Scale are introduced, and the study protocol for their validation is presented.

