##### Data analysis

Selectivity and sensitivity will be assessed using the same cut-off values for individual test items, and the same three pass/ fail criteria determined in the original study by Hoche et al. [10] (that is: possible CCAS = one test failed; probable CCAS = two tests failed; definite CCAS = three or more tests failed). To assess selectivity the percentage of true negatives will be calculated, that is the percentage of controls which have been correctly identified as controls [number of controls identified as controls/ true number of controls in the sample * 100]. To assess sensitivity the percentage of true positives will be calculated, that is the percentage of patients which have been correctly identified as patients [number of patients identified as patients/ true number of patients in the sample * 100]. In case selectivity and sensitivity falls below the values of the original CCAS Scale, selectivity and sensitivity of individual tests will be assessed. Cut-off values of single test items and/ or cut-offs defining (possible/ probable/ definite) CCAS will be adjusted to achieve high selectivity and reasonable sensitivity – comparable to the values of the original CCAS Scale.

Differences between patient groups (pure cerebellar disease vs. patients with additional extracerebellar involvement) will also be analyzed. We want to verify that difficulties in verbal registration and delayed verbal recall are indicative of extracerebellar involvement (“red flags”). In further accordance with Hoche et al. [10], Cronbach’s alpha will be used to assess the inter-relatedness of the individual test items, i.e. internal consistency.

To study construct validity of the CCAS Scale subtests of validated German versions of neuropsychological test batteries will be used as the external criterion. We will compare the percentage of patients diagnosed with CCAS based on a detailed neuropsychological test battery with the percentage of patients identified by the CCAS Scale.

Finally, correlations between age, disease duration, severity of cerebellar motor symptoms (measured by clinical ataxia scores), and total CCAS sum score will be calculated. All raw data (thus total number of failed tests respective total sum score and sub scores on single test items) will be tested for normal distribution using Kolmogorov-Smirnov tests. Parametric or non-parametric tests will be applied depending on distribution and final sample size.

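### The rule for revising cut-offs sets German point estimates against six US point estimates, allows for no sampling error, and does not say which of the six must fall short

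*Protocol article*

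**What the plan says.** The abstract sets the aim: "We test whether selectivity and sensitivity of the German CCAS Scale is comparable to the original CCAS Scale", using the US item cut-offs and pass/fail criteria. The Data analysis section names the three tiers as "possible CCAS = one test failed; probable CCAS = two tests failed; definite CCAS = three or more tests failed" and defines selectivity and sensitivity as simple percentages of controls and patients correctly classified.

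The decision rule follows: "In case selectivity and sensitivity falls below the values of the original CCAS Scale, selectivity and sensitivity of individual tests will be assessed". The next sentence says that item cut-offs and/or the cut-offs defining CCAS "will be adjusted to achieve high selectivity and reasonable sensitivity – comparable to the values of the original CCAS Scale".

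The benchmarks stand in the Background. Selectivity is "possible/ probable/ definite CCAS: 78/ 93/ 100" percent and sensitivity is "possible/ probable/ definite CCAS: 95/ 82/ 46" percent, from a validation sample of "39 adult cerebellar patients, including patients with cerebellar degeneration and focal cerebellar lesions and 55 matched healthy controls". The Study sample section plans at least 65 patients and as many matched controls for version A. No interval, margin or test is attached to the rule.

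**The concern.** An observed percentage from 65 people will fall below its own true value roughly half the time. A rule that reacts to any shortfall against a fixed figure therefore reacts to chance. Here the fixed figures are themselves estimates from small samples, and there are six of them.

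The rule also leaves open what counts. It joins the two measures with an *and*, names three tiers, and does not say whether any, some or all of the six values must be low.

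The rule bears on the main question of the validation, namely whether the US criteria carry over to German. If cut-offs move because of noise, German and US classifications stop being equivalent for no real reason. The Perspective section foresees using the scale for patient characterization and stratification in later therapeutic trials, where that equivalence matters.

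**Working it through.** The article states no error rate or sample-size derivation, so there is no design figure to reproduce.

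**Benchmarks (Background).** All six match whole counts. The intervals are exact 95% intervals.

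| Measure | Tier | Count | Percent | 95% interval |
|---|---|---|---|---|
| Sensitivity | possible | 37/39 | 95 | 83–99 |
| Sensitivity | probable | 32/39 | 82 | 67–93 |
| Sensitivity | definite | 18/39 | 46 | 30–63 |
| Selectivity | possible | 43/55 | 78 | 65–88 |
| Selectivity | probable | 51/55 | 93 | 82–98 |
| Selectivity | definite | 55/55 | 100 | 94–100 |

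**Model.** n = 65 per group, and true German values equal the US ones. The tiers are nested, so each group is one multinomial over 0, 1, 2 and 3 or more failed tests:
- Patients: 0.05, 0.13 (95 − 82), 0.36 (82 − 46), 0.46.
- Controls: 0.78, 0.15 (93 − 78), 0.07 (100 − 93), 0.

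**Each benchmark alone.** P(X < 65p), with X ~ Bin(65, p):
- Sensitivity possible: 65 × 0.95 = 61.75, so P(X ≤ 61) = 41%.
- Sensitivity probable: 53.3, P(X ≤ 53) = 51%.
- Sensitivity definite: 29.9, P(X ≤ 29) = 46%.
- Selectivity possible: 50.7, P(X ≤ 50) = 47% (0.465).
- Selectivity probable: 60.45, P(X ≤ 60) = 48%.
- Selectivity definite: 0%, because a true 100% cannot be missed.

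**Combined, with nesting kept.** At least one sensitivity value is below in 74.3% of studies, and at least one selectivity value in 63.5%. If observed values are first rounded to whole percent, these become 70.6% and 63.5%. The groups are independent, which gives the first two rows. The others come from simulation (400,000 draws).

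| What must fall below | Unrounded | Rounded |
|---|---|---|
| Any one of six | 1 − 0.257 × 0.365 = 90.6% | 1 − 0.294 × 0.365 = 89.3% |
| At least one of each measure | 0.743 × 0.635 = 47% | 0.706 × 0.635 = 45% |
| Both at the same tier | 34% | 30% |
| All five that can be missed | 5.6% | 4.9% |
| All six | 0% | 0% |

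Under the any-of-six reading, adding the sampling error of the US values raises the unrounded figure to 92.7%.

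**The 100% benchmark.** It adds nothing to the figures above. If true definite selectivity is below 100%, one control with three failed tests breaches it. At a true 99% the chance is 1 − 0.99^65 = 48%; at 98% it is 73%.

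**Precision available.** The half-width of the 95% CI for German minus US is 1.96 × √[p(1 − p)(1/65 + 1/m)], with m = 39 for patients and 55 for controls. Sensitivity gives 8.7, 15.3 and 19.8 points (possible, probable, definite). Selectivity gives 14.9 and 9.2 (possible, probable).

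**The case against.** The strongest reply is that the sentence says selectivity *and* sensitivity. On that wording a shortfall in a single figure does not meet the rule, and the chance rate is 45–47% or 30–34%, or near zero if every value must fall. This stands, and it rules out any unconditional statement that the rule fires nine times in ten. It does not rescue the rule: the text does not choose among these readings, and both of the milder *and* readings still give rates far above a usual error level.

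A second reply is that the quoted sentence triggers only an item-level look, that the adjustment aims at comparable rather than equal values, and that the Perspective section says only that cut-offs may change. This stands in part. Automatic revision after a one-participant shortfall is one reading, not the declared rule. Still, the adjustment sentence follows directly and attaches no size of shortfall to it.

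A third reply is that intervals and margins may sit in an analysis plan that is not shown. That would excuse silence. The article is not silent, however: it states a decision rule and states it without allowance for error.

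A reader might also infer from the tier labels that the tiers are mutually exclusive, so that a perfect replica would show 13/36/46 in patients. The documents do not support that. The Background prints the same labels beside 95/82/46, which sum to 223 and so must be cumulative, and the analysis adopts the original criteria. It is a wording point only.

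**Conclusion.** The point holds in conditional form. As written, the rule treats six imprecise US percentages as exact thresholds and leaves open which must be missed. For a scale that performs exactly like the original, the chance of meeting it runs from about 90% to zero depending on the reading. On the two middle readings, which follow the *and* in the text, it is about 30–47%.

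These figures assume the minimum of 65 per group, nested tiers and true values equal to the published percentages. Larger samples barely help: the any-of-six rate stays at 87–92% for 80 to 130 per group.

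A reader might infer that the US criteria would almost always be rejected by chance, or that even a better scale would usually fail. The documents do not support either without the any-of-six condition. For a scale truly 3 points better on every figure below 100%, the rate is about 56–60% under any-of-six, but 11–13% if one of each measure must fall and 3–4% at the same tier.

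**What to change.** Change the Data analysis text, before the data are analysed, as follows:

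1. Word the tiers as at least 1, at least 2 and at least 3 failed tests.
2. State which of the six percentages decide, and whether any or all of them must fall short.
3. Replace the bare comparison with a prespecified margin, judged with the 95% CI for German minus US and with both samples treated as random (US counts 37, 32 and 18 of 39; 43, 51 and 55 of 55). A score-based interval is needed for the 100% benchmark, because the simple Wald interval has zero width when both samples show 100%.
4. Claim comparability only where the CI excludes a loss larger than the margin. Report a CI that includes both no loss and a larger loss as inconclusive: neither proof of comparability nor an automatic reason to change cut-offs.
5. Report all six differences with their CIs.

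Revising only when the CI lies wholly below zero would not be enough. On probable sensitivity, with the US result at 32/39, a true 15-point loss would be picked up in only about 29% (Newcombe interval) to 38% (Wald interval) of studies, and the rest would be read as comparable.

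The change needs a few sentences and no new data. The cost is candour: with half-widths of about 9 to 20 points, some comparisons will be inconclusive. Even at an observed difference of zero, a margin narrower than the half-width cannot be met.

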##### Study sample

For validation of version A at least 65 patients and an equal number of matched healthy controls will be recruited. About one third (≥ 25) of the patients will suffer from disorders that primarily affect the cerebellum (isolated cerebellar disease = cer-pure: 1. degenerative cerebellar disorders, e.g. spinocerebellar ataxia type 6 (SCA6); 2. focal cerebellar lesions, e.g. cerebellar stroke). The other two thirds (≥ 40 patients) will suffer from disorders with additional extracerebellar involvement (cerebellar plus disease = cer-plus: 1. degenerative cerebellar disorders, e.g. SCA1, 2 or 3; 2. focal cerebellar lesions, e.g. cerebellar stroke with additional involvement of the brain stem). Group assignment in patients with cerebellar degeneration goes by diagnosis: A genetic disease, which is known to involve extracerebellar regions, is considered a “cer-plus form”, although the clinical phenotype at the time of testing may be pure cerebellar.

An equivalent number of healthy matched participants will serve as controls. Each patient will be matched with a control participant of same sex, similar age (interval: +/− 5 years) and similar years of education (intervals: < 9 yrs., 9–10 yrs., 11–13 yrs., 14–16 yrs., > 16 yrs.). We will use the same matching criteria as in [10] except for education matching because of the different educational systems in Germany and the United States.

Parallel versions B-D will be validated in groups of 25 patients (cer-pure and cer-plus, respectively) and 25 matched healthy controls each.

Patients in this investigator-initiated, multicenter study will be recruited from the ataxia clinics at the Departments of Neurology of the University Hospitals in Aachen, Bonn, Duesseldorf, Essen, Heidelberg and Tuebingen, as well as from the MediClin Fachklinik Rhein-Ruhr in Essen, and the Departments of Neurosurgery of the University Hospital in Essen and at the Klinikum Dortmund. Essen is the coordinating site. Furthermore, we will collaborate with the “Deutsche Heredo-Ataxie Gesellschaft e.V. (DHAG)”, a patient support group, and patients will be recruited via their newsletter and webpage. Healthy controls will be recruited from patients’ families and by public bulletins.

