##### Assessment of the CCAS Scale

The CCAS Scale will be administered in each participant at least once. In the validation process of version A, at least 40 patients and 40 controls will receive a follow-up examination with the same version of the scale to determine test-retest and interrater reliability (≥ 20 patients and ≥ 20 controls, respectively). Retesting will be done with the same version because equivalence of versions A-D has not yet been shown (see [10] and Supplements). Follow-up will take place within an interval of 14 to 56 days. A time interval is favored instead of a fixed time span between test and retest (e.g. exactly 14 days) to control for learning effects by correlating retest results with different retest time intervals.

To assess construct validity of the German version of the CCAS Scale a detailed neuropsychological testing will be done in a subset of patients (*n* ≥ 20) and controls (*n* ≥ 20) using well-established neuropsychological test batteries available in German. These will comprise the logical memory test (part I and II) of the Wechsler Memory Scale – 4th edition (WMS-IV) [18], the copy immediate and delayed recall of the Rey–Osterrieth Complex Figure Test (ROCFT) [19], and the letter-number sequencing task of the WAIS-IV [20]. These tests measure the same cognitive domains as corresponding items of the CCAS Scale. Furthermore, the German version 3 of the MoCA [21] will be assessed for direct comparison with the CCAS Scale. Finally, the Patient Health Questionnaire (PHQ-9) [22] and the German version of the EuroQuol – 5 dimension – 3 level (EQ-5D-3L) questionnaire [23] will be administered.

Validation of parallel versions of the CCAS Scale will be done the same way as for validation of parallel German versions of the MoCA [21]. Each parallel version (B/C/D) of the CCAS Scale will be tested against version A. Testing of version B/C/D and version A will be done on the same day, with the order being randomized between participants.

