## Perspective

Clinical ataxia scales have been validated to rate the severity of motor symptoms in cerebellar disease [13–17], but so far there has not been a validated clinical scale to screen for the presence of the Cerebellar Cognitive Affective/ Schmahmann Syndrome (CCAS), and quantify CCAS severity. Only recently, Schmahmann and collaborators have developed and validated a promising screening tool for the CCAS – the CCAS Scale – for an American English-speaking population [10]. Till now, no validated German versions of the scale exist. German versions of the CCAS Scale are highly desirable to screen for the presence of CCAS in a clinical setting, but also for patient characterization and stratification in future therapeutical trials. The CCAS sum score may also serve as a therapeutic marker, but this would need future studies to show its sensitivity to change, and if this would be the case, its treatment responsiveness. In this multicenter study, four parallel versions (A-D) of the German CCAS Scale will be validated in a large cohort of German-speaking patients with cerebellar disorders. The parallel versions will allow multiple testing without practice effects.

The primary aim of our validation study is to show high selectivity, that is to show that the German versions of the scale are able to differentiate between patients and controls. We will test whether the pass/ fail criteria used to determine the presence of CCAS in the original scale also apply for the German scale. Cut-off values of individual test items and the pass/ fail criteria shown in Fig. 1 are taken from the US-American original and may change depending on findings in the German validation cohort. Furthermore, future studies are needed to test for possible age effects, and the need for age-dependent cut-off values and pass/ fail criteria. After full validation of the scale the implementation of a web-based training tool is planned.

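### If the US cut-offs fall short, revised cut-offs are chosen and scored on the same 65 + 65 people, so the accuracy of the revised German scale would be optimistic

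*Protocol article*

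**What the plan says.** The protocol article, Data analysis, sets out two steps.

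- **Step 1, unchanged criteria.** "Selectivity and sensitivity will be assessed using the same cut-off values for individual test items, and the same three pass/ fail criteria" of the original study are applied to the German sample.
- **Step 2, conditional.** "In case selectivity and sensitivity falls below the values of the original CCAS Scale, selectivity and sensitivity of individual tests will be assessed". Then: "Cut-off values of single test items and/ or cut-offs defining (possible/ probable/ definite) CCAS will be adjusted to achieve high selectivity and reasonable sensitivity", with the aim of results "comparable to the values of the original CCAS Scale".

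The Perspective section names the data that drive any change: item cut-offs and pass/fail criteria "may change depending on findings in the German validation cohort". It also gives the goal: "The primary aim of our validation study is to show high selectivity".

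The size of that cohort is in Study sample: "For validation of version A at least 65 patients and an equal number of matched healthy controls will be recruited". The other data collections described have other purposes. The retest serves reliability. The groups of 25 patients and 25 controls for versions B to D serve the comparison of each parallel version with version A: "Testing of version B/C/D and version A will be done on the same day, with the order being randomized between participants".

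**The concern.** Step 2 uses one cohort both to choose the cut-offs and to score them. Selectivity and sensitivity calculated after the adjustment are resubstitution estimates. The search keeps whichever cut-offs happen to suit these particular people, and part of that fit will not recur in new patients and controls.

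Two features make this more than a remote possibility. The trigger is a bare comparison of point estimates, with no margin or interval, against benchmarks from only 39 patients and 55 controls. The wording also leaves open whether one measure or both must fall short, and at which of the three CCAS levels.

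At stake are the figures that would accompany any revised German cut-offs. The Perspective section foresees use of the scale for clinical screening and for stratification in future trials. Revised cut-offs whose accuracy is quoted without correction would be expected to do less well there than stated.

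**Working it through.** **1. Inputs.** Background gives US selectivity of 78/93/100% (possible/probable/definite) in 55 controls, US sensitivity of 95/82/46% in 39 patients, and Cronbach's alpha of 0.59. Study sample gives n = 65 per group. The article states no precision target or margin with that number, so there is no sample-size figure to reproduce.

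**2. Reproducing the US percentages.** They fit whole-number counts, which are inferred here. Intervals are Clopper-Pearson 95%.

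| Criterion | Selectivity (n = 55) | Sensitivity (n = 39) |
|---|---|---|
| Possible | 43/55 = 78.2% (65.0 to 88.2) | 37/39 = 94.9% (82.7 to 99.4) |
| Probable | 51/55 = 92.7% (82.4 to 98.0) | 32/39 = 82.1% (66.5 to 92.5) |
| Definite | 55/55 = 100% (93.5 to 100) | 18/39 = 46.2% (30.1 to 62.8) |

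**3. Chance of triggering step 2 when the scale transfers perfectly.** Set the true German accuracy equal to the US estimate p, and let X be binomial(65, p). The measure falls short when X < 65p.

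- Probable selectivity: 65 × 51/55 = 60.27, so it falls short at X ≤ 60, with probability 0.515.
- Probable sensitivity: 65 × 32/39 = 53.33, so it falls short at X ≤ 53, with probability 0.508.
- Possible selectivity 0.451, possible sensitivity 0.429, definite sensitivity 0.452. Definite selectivity is left out, because a true value of 100% cannot fall short.

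For the probable criterion, treating patients and controls as independent:

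- Both fall short: 0.515 × 0.508 ≈ 0.26.
- At least one falls short: 1 − (1 − 0.515)(1 − 0.508) ≈ 0.76.

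**4. Size of the optimism.** The article does not say how cut-offs would be searched, so two searches were simulated. Both assume ten normally distributed, equally correlated items and 65 + 65 people. Tuned cut-offs were then scored in 20,000 new patients and 20,000 new controls.

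*Search A* adjusts item cut-offs to close shortfalls against the US percentages. The inter-item correlation r = 0.126 reproduces alpha: 10 × 0.126 / (1 + 9 × 0.126) = 1.26/2.134 = 0.59. There were 100 replicates.

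| Average patient shift | Probable selectivity/sensitivity, in sample | In new people | Loss (points) | Possible selectivity, in sample → new |
|---|---|---|---|---|
| 0.7 SD | 84.8/75.0 | 78.9/69.3 | 5.9/5.7 | 51.6 → 43.5 (8.1) |
| 1.0 SD | 92.6/78.8 | 89.6/73.6 | 3.0/5.2 | 67.7 → 60.3 (7.4) |
| 1.3 SD | 95.7/83.2 | 94.9/80.6 | 0.8/2.6 | 78.8 → 74.1 (4.7) |

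*Search B* maximises the Youden index at two or more failed tests, with correlation 0.13 or 0.3 and 150 replicates. For shifts from 0 to 1.1 SD, the losses were 8.1 to 10.6 points of sensitivity and 8.4 to 10.9 points of selectivity. At 0.8 SD and correlation 0.13, sensitivity/selectivity was 83.6/84.1 in sample and 73.5/75.2 in new people.

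The direction is the same in every setting. The size runs from about 1 to about 10 points per measure (0.8 to 10.9).

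**The case against.** The strongest reply is that the plan tests the unchanged US criteria first, on people who had no part in choosing them. That stands. A reader might infer that the study could no longer say whether the US criteria carry over. The documents do not support this, because step 1 answers that question and step 2 is only conditional.

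A reader might also infer that the primary aim becomes circular, since any scale can be loosened until its own controls pass. This goes too far as well. The target joins high selectivity with reasonable sensitivity, so loosening has a price. In search A, in-sample 'possible' selectivity stayed at 51.6% and 67.7% in two of three settings, short of 78%.

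The size is also open to challenge, and that stands. Ten items, the shift, the use of alpha as a within-group correlation and an exhaustive search are all assumptions. The article mentions neither search, and changing one or two cut-offs would give less optimism. In the setting closest to the US 'probable' figures (1.3 SD) the loss is 0.8 and 2.6 points. By comparison, the 95% interval for 60/65 is 83.0 to 97.5%.

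Finally, it can be said that resampling methods belong in a full protocol or analysis plan that is not shown. Their absence from an article is indeed no error. What the article does fix is the adjustment, its target and the sample, and following those words exactly gives a biased figure for the revised scale.

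**Conclusion.** The point holds for the revised cut-offs only. If step 2 is carried out as written, the accuracy of the revised scale is resubstitution accuracy and will be too favourable. The step 1 result is unaffected.

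The trigger is weak. Even with perfect transfer, each 'probable' measure falls short about 51% of the time. For that criterion, re-tuning would start by chance in about 26% of studies if both measures must fall short, or about 76% if either suffices. These figures take the US point estimates as the truth and treat the two groups as independent.

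The direction of the bias is secure. Its size, roughly 1 to 10 points per measure, rests on the simulated item model, patient shift and search, and should be read as a range rather than an estimate. Harm in practice needs three things: cut-offs are revised, their accuracy is not corrected, and they are adopted.

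**What to change.** 1. State that the result with the unchanged US cut-offs and pass/fail rule, with 95% confidence intervals, is the primary validation result and is reported whatever it shows.
2. Define the trigger for revision: which CCAS level, one measure or both, and by what margin.
3. Label any revised cut-offs as derived, not validated. Report their selectivity and sensitivity only after bootstrap or repeated cross-validation that repeats the whole cut-off search in each resample. A simple split is less attractive: search B with 32 per group (0.8 SD, correlation 0.13) lost 13.3 points of sensitivity and 12.4 of selectivity.
4. Treat a check on version A results from the B/C/D participants as supportive only. It can use people who are not in the 65 + 65 and who took version A first. With random order, that is at most about 3 × 25 / 2 ≈ 37 per group. At 34/37 the 95% interval is 78.1 to 98.3%, too wide to show a loss of a few points. The article does not say whether these people overlap with the 65 + 65; if they do, rely on the resampled figures alone.

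The cost is wording, a few hours of analysis and slightly lower quoted accuracy for any revised cut-offs. No new participants are needed.
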